## Abstract

**Background:**

Complications of exposure to second-hand smoke (SHS) are known to affect the health of pregnant women; it requires designing an educational program to reduce the exposure of pregnant women to smoke. Therefore, the purpose of this study was to design an educational program to reduce the exposure of pregnant women with the second-hand smoke of their husband.

**Methods:**

This research-based program is designed in three phases, in the first phase of the study, the level of knowledge, attitude, and practice of men regarding SHS will be measured using a questionnaire. The questionnaire will be based on a literature review and experts opinions. In the next phase the educational program will be designed based on the results of the first phase of the study on the level of knowledge, attitude, self-efficacy, and practice of men, as well as a literature review and experts opinions, and the research team will finalize it according to priorities. To follow up the training will be sent reminders messages. Pregnant women will also be trained to protect themselves and support their husbands to quit smoking. The third phase includes the implementation of educational intervention with pretest-posttest with two intervention and control groups.

**Discussion:**

The present study provides strong information and data regarding the needs and strategies for reducing the exposure to second-hand smoke in pregnant women. Therefore, designing a program, and a review article and updated evidences can lead to avoid pregnant women the exposure to second hand smoke and reducing smoking in smoker husbands. It can also reduce their medical and treatment costs.

**Trial registration:**

Registration of this randomized control trial has been completed with the Iranian Registry of Clinical Trials, IRCT20180722040555N1.

## Plain English summary

Second-hand smoke exposure is a risk factor for the health of pregnant women, and associated with dangers such as preterm labor, rupture of membranes, cesarean delivery, decreased growth, and intrauterine growth retardation, fetal weight loss, and so on. The exposure to smoke is including breathe of smoke from burning cigarette and smoke from exhaling of smokers. Although the prevalence of female smokers is low in Iran, the high prevalence of smoking among men put women at the risk of SHS. The aim of this study was to design an educational intervention on the smoke of SHS in smoker men on the exposure of pregnant wives. This research-based program is designed in three phases, in the first phase of the study; the level of knowledge, attitude, and practice of men regarding SHS will be measured using a questionnaire. The questionnaire will be based on a literature review and experts opinions. In the next phase the educational program will be designed based on the results of the first phase of the study on the level of knowledge, attitude, self-efficacy, and practice of men, as well as a literature review and experts opinions, and the research team will finalize it according to priorities. To follow up the training will be sent reminders messages. Pregnant women will also be trained to protect themselves and support their husbands to quit smoking. The third phase includes the implementation of educational intervention with pretest-posttest with two intervention and control groups. In the pretest phase, questionnaires will be completed by men and the exposure of women to SHS will be achieved as self-reported. Two months after the training in the post-test phase, the questionnaire will be completed again by men. The exposure of pregnant women to SHS and the amount of salivary cotinine will be measured.

## Background

Smoking is an important risk factor for health and development [1]. Smoking habits are seen among various social groups so that about 50% of men in developing countries smoke and 35% in developed countries [2]. The exposure to smoke is including breathe of smoke from burning cigarette and smoke from exhaling of smokers ([3], https://www.cdc.gov/tobacco/data_statistics/fact_sheets/secondhand_smoke/general_facts/). In the world, more than 40% of children, 33% of non-smokers men and 35% of non-smokers women are exposed to SHS [4–6]. Predicted, by 2030 the death rate from tobacco will be more than 8 million, which approximately 5.2 million are women [2]. Although the prevalence of female smokers is low in Iran, the high prevalence of smoking among men put women at the risk of SHS [7], more than half of Iranian women, during pregnancy (56.2%) were exposed to second-hand smoke [8]. Exposure to SHS can lead to ischemic heart disease, respiratory infections, asthma, and lung cancer [4]. Complications, especially in pregnant women, are significant, such as preterm labor [9–13], rupture of membranes [14], cesarean delivery [10], decreased growth, and intrauterine growth retardation [2, 9, 13], low birth weight fetus [9, 11–13], distress fetus [11, 12], small fetus compared to gestational age [10], Sudden infant death syndrome and increasing the Cotinine level in follicular fluid in women were exposed to SHS [15]. Husband’s smoking is a source of tobacco smoke exposure at home [16]. The only way to protect non-smokers is to reduce smoking in the home, the work environment, and the general environment, and the highest exposure to SHS occurs at home (https://www.cdc.gov/tobacco/data_statistics/fact_sheets/secondhand_smoke/general_facts/). Effective interventions to reduce exposure to SHS in pregnant women are necessary and the content of these interventions should be for both pregnant women and their husbands [6]. Wakefield reported that creating messages that raise awareness and acceptance of the risks of exposure to SHS in pregnancy and childhood, may increase the incentive of men to quit smoking and that encouraging men to participate and support their wife during pregnancy, finally will lead them to quit smoking [17]. Educational interventions for smoking could reduce smoking rates for men during the pregnancy of his wife; therefore, pregnancy can be a motivating factor for changing the behavior of smoker men [18], and husbands’ awareness of the risks and prenatal care is effective in contributing to the health of pregnant women [19]. Therefore, interventions should be designed, in addition to raising knowledge and changing the attitude and practice of smoker husbands towards cigarette smoking, can reduce exposure to SHS in pregnant women. The purpose of this study was to design an educational program about SHS in smoker men on the exposure of their pregnant wives.

## Methods/design

This research-based program is designed in three phases, in the first phase of the study; the level of knowledge, attitude, and practice of men regarding SHS will be measured using a questionnaire. The questionnaire will be based on a literature review and experts opinions. In the next phase the educational program will be designed based on the results of the first phase of the study on the level of knowledge, attitude, self-efficacy, and practice of men, as well as a literature review and experts opinions, and the research team will finalize it according to priorities. To follow up the training will be sent reminders messages. Pregnant women will also be trained to protect themselves and support their husbands to quit smoking. The third phase includes the implementation of educational intervention with pretest-posttest with two intervention and control groups.

## Aim

In this study, we are looking at designing an educational program on SHS in the smoker men, in addition to raising knowledge and changing the attitude and practice of smoker husbands towards cigarette smoking, can reduce exposure to SHS in pregnant women.

## Research hypotheses

According to the main purpose of the study, hypotheses will be considered according to the views of health education and reproductive health professionals. The mean score of knowledge, attitude, and practice of smokers after intervention in the intervention group will be more than the control group. The mean of salivary cotinine and the average number of cigarettes that exposed to them during one week in pregnant women after intervention in the intervention group will be less than the control group.

### Phase I: Designing a questionnaire on knowledge, attitude and practice of smoker men

First, a literature review will be done to select the appropriate model, after interviewing the panel of health education professionals, promotion of health, psychology, epidemiology and reproductive health and reviewing the studies, the questionnaires will be designed based on some of the constructs of the health belief model. The questionnaire consists of the following structures: knowledge, perceived sensitivity, perceived severity, self-efficacy, and behavior. To assess the validity of the questionnaire, a fifteen-person panel of health education professionals, health promotion, psychology, epidemiology and reproductive health will be used and CVR and CVI will be obtained to verify structures. To verify the reliability of the questionnaire, internal consistency with alpha Cronbach will be measured. The questionnaire will be used in the pre-test and post-test of the intervention phase.

### Phase II: Designing an educational intervention

The design of the intervention and the target audience’s recognition, at this stage, will be based on a review of the literature, studying the similar studies, as well as information from the questionnaire designed in the previous phase. In this study, the educational package with regard to time limitation of contacts includes lecture sessions (30–60 min), educational pamphlets, animations about second-hand smoke harms, fetus photos, reminiscent text messages and the training of pregnant women to support their husband for reducing smoking. Types of educational messages are listed in Table 1.

**Table 1 Tab1:** Types of educational package messages

*• Educational messages*: Content about cigarette smoke, SHS and its complications presented at a lecture and pamphlet (e.g. SHS causes preterm labor).	
**•** *Functional messages*: Describe the simple steps to quit smoking and protect your wife from smoke presented at a lecture and pamphlet (e.g. put lighter and ashtray away from your reach).	
**•** *Motivational messages*: Includes images and animations (examples: images included in the pamphlets and animations related to cigarettes and its effects).	
**•** *Self-efficacy promotion messages*: Breaking complex behaviors into simple steps, presented in Pamphlet and use the role model at a lecture session (e.g. Simple steps to quit smoking and protective strategies, key sentences about the ability to quit smoking, expressing the experiences of a smoker from the history of smoking cessation and having the ability to quit smoking).	
**•** *Alert or reminder messages*: Message or content to remind you of second-hand smoke complications for pregnancy and embryos (including a picture will be given to the participants to sit at their home in front of their eyes; this photo is “a fetus who asks the father not to smoke” and sending reminders).	
**•** *Supportive messages*: Getting help from pregnant women as “educational co-sponsors” to support their husbands to quit smoking.	

#### Training session (lecture, pamphlets, and expressions of experiences of people with a history of smoking cessation)

The lecture will contain information on pregnancy and childbirth, cigarette smoke, and the diagnosis of all types of smoke and second-hand smoke complication for pregnancy and fetuses and recommendations for the protection against smoke. It will be presented as a lecture to raise knowledge and attitudes. Animation, educational pictures and educational pamphlets will be used to motivate. Simple steps to stop smoking and to express the experiences of a smoker, who has previously had a history of cessation of smoking, will be used to increase self-efficacy.

#### Follow up and maintaining education (fetus photo, SMS reminder, receiving support from pregnant women)

At the end of the lecture, a picture will be given to the participants to sit at their home in front of their eyes; this photo is “a fetus who asks the father not to smoke”. After training, for two months at the end of each week, an alert SMS will be sent to the participants. Pregnant women will be trained to protect against second smoke and support their husbands to quit smoking. Pregnant women will be as “educational co-sponsors”.

## Experts’ team

The content and visual validity of the questionnaire and educational program will be measured, and the comments received from the panel of experts. The panel of experts will be included eight professionals from health education, one expert from the health promotion field, one expert from the epidemiology, four professionals from the reproductive health and one expert from the field of psychology.

### Phase III: Implementation of educational intervention

In this step a randomized controlled clinical trial will design to assess the efficacy of prepared protocol. Participants randomly will allocate into two groups. In experimental group we will implement our designed protocol, and control group will not receive any intervention, but they follow as same as experimental group. For ethical issues all educational material will offer them at the end of study.

#### Study environment and population

This interventional randomized study will be conducted at health centers of Isfahan, Iran.

#### Study sample

This interventional randomized study will be conducted on smoking men who have exposed their pregnant wives to cigarette’s smoke and their wives have been receiving maternity care at health centers of Isfahan, Iran.

#### Sampling method

Convenience sampling’s method will apply to select the participants. The sampling method will be random and the participants will be in two groups of intervention and control.

#### Inclusion criteria

Inclusion criteria are smoker men with pregnant women aged between 15 and 49 years, the men who smoke at least one cigarette daily beside their pregnant wives, Iranian nationality, consent to participate in the study, ability to understand questions or ability to read and write, not participating in any other clinical trials at the same time.

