#### Exclusion criteria

The exclusion criterion is not completing the intervention for any reason, the smoker men who are not with their pregnant wives for more than one week, the pregnant termination, and the death of the spouse or immigration and active smoker women and presence of other sources of exposure such as other smokers at home, smoke exposure at work, women’s active smoking, etc.

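### Eligibility sets no upper gestational age, yet exposure and cotinine are to be measured in pregnant women two months after training, so some women are expected to deliver first

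*Protocol article*

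**What the plan says.** The Inclusion criteria section of the protocol article gives an explicit list. On the wife's pregnancy it says only: "Inclusion criteria are smoker men with pregnant women aged between 15 and 49 years". The Study sample section adds that "their wives have been receiving maternity care at health centers of Isfahan, Iran". Neither section, nor any other, names a trimester, an antenatal visit or a gestational age at entry.

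The timing of follow-up is in the Plain English summary: "Two months after the training in the post-test phase, the questionnaire will be completed again by men", followed by "The exposure of pregnant women to SHS and the amount of salivary cotinine will be measured". The section on follow-up and maintaining education gives the reminder component the same length: "After training, for two months at the end of each week, an alert SMS will be sent to the participants".

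The Research hypotheses section places the women's outcomes in pregnancy and after the intervention: "The mean of salivary cotinine and the average number of cigarettes that exposed to them during one week in pregnant women after intervention". According to Data collection method, exposure is asked about before and after the intervention, whereas cotinine is measured only after it.

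The Exclusion criteria include "the pregnant termination", and open with "The exclusion criterion is not completing the intervention for any reason". Delivery is neither named nor exempted.

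**The concern.** The entry rule admits couples at any stage of pregnancy, but two of the outcomes need the woman to be still pregnant about two months after training. For couples who join late, the two requirements cannot be expected to hold together. A couple at 36 weeks meets the inclusion criteria as written and would be expected to have a newborn at the post-test.

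Such a woman either contributes no exposure or cotinine value, or contributes one taken postpartum. In the first case the trial loses evaluable couples whom it has randomised and trained. Cotinine has no pre-test value, so a woman without a post-test sample adds nothing to that comparison. In the second case the mean compared between arms is a blend of pregnant and postpartum values, which is not the quantity in the hypothesis. A pregnancy measurement missed for this reason cannot be recovered later.

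**Working it through.** The article states no sample size, power, dropout allowance or gestational age at entry, so it offers no figure to reproduce. The check is one of timing, followed by an illustration of size.

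**Inputs**
- Interval from training to post-test: two months (Plain English summary), taken as 60.9 days.
- Upper gestational age at entry: none stated (Inclusion criteria).
- Gestational age at delivery: not in the article. Assumed 40 weeks, with 37 weeks as the alternative.
- Gestational age at entry: not in the article. Assumed uniform between a start week and an end week.

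**Step 1. Latest gestational age at training**

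Interval = 60.9 / 7 = 8.7 weeks.

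Limit = gestational age at delivery − 8.7 weeks:
- delivery at 40 weeks: 40 − 8.7 = 31.3 weeks
- delivery at 37 weeks: 37 − 8.7 = 28.3 weeks

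This limit applies at training. Any gap between pre-test and training leaves it unchanged but lowers the corresponding limit at pre-test by the length of the gap. With a gap of two weeks, for example, the limits at pre-test are 29.3 and 26.3 weeks.

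**Step 2. Illustrative share past the limit**

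With uniform entry, delivery at 40 weeks and no gap before training, share = (end − 31.3) / (end − start).

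| Entry window (weeks) | Calculation | Share |
|---|---|---|
| 6 to 36 | 4.7 / 30 | 16% |
| 8 to 38 | 6.7 / 30 | 22% |
| 8 to 40 | 8.7 / 32 | 27% |
| 16 to 40 | 8.7 / 24 | 36% |

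For start weeks 6 to 16 and end weeks 36 to 40, the first and last rows are the extremes.

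**Step 3. Sensitivity to variable delivery dates**

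A simulation drew delivery from a Normal distribution (mean 39.5 weeks, SD 1.8, both assumed) and entry uniformly from 6, 12 or 20 weeks up to a cap. Women already delivered at entry were left out. The table gives the share delivering before the post-test, with no gap between entry and training.

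| Latest entry (weeks) | From 6 | From 12 | From 20 |
|---|---|---|---|
| 40 | 24.8% | 30.5% | 43.3% |
| 32 | 5.7% | 7.4% | 12.4% |
| 30 | 1.6% | 2.2% | 3.9% |
| 28 | 0.2% | 0.3% | 0.6% |

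With a two-week gap between entry and training, the 28-week row becomes 1.8%, 2.4% and 4.9%.

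**Step 4. What a loss of this size would cost**

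Enrolment needed per 100 evaluable = 100 / (1 − loss), rounded up. A 16% loss needs 100 / 0.84 = 120, a 25% loss needs 100 / 0.75 = 134, and a 36% loss needs 100 / 0.64 = 157.

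**The case against.** The strongest reply is that this is a gap in a condensed article: a gestational window, or a rule for women who deliver early, may stand in the full protocol. That has some weight. But the article sets out its eligibility criteria as a list, and that list as printed does not fit the outcome definition.

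Several stronger readings are tempting, and the document does not support them.

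- A reader might infer that delivery is itself an exclusion, so that these women will be dropped. The wording "the pregnant termination" may mean pregnancy loss only. What can be said is that its scope is unclear.
- A reader might infer that every outcome is lost. The men complete the knowledge, attitude and practice questionnaire, and can do so after the birth. A delivered woman can also still answer questions and give saliva, so her value may be postpartum rather than missing.
- A reader might infer bias between the arms. Gestational age at entry is fixed before randomisation and should balance on average. The article does list preterm labour among the complications of exposure, and exclusion for not completing the intervention could work differently in untreated controls. Neither route is given a size, so bias is possible but not shown.
- A reader might infer that the control post-test has no date, because controls receive no training. The Phase III section says controls are followed in the same way as the experimental group, which is an adequate statement for an article.
- A reader might take the percentages as a forecast. They rest wholly on the assumed entry pattern.

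**Conclusion.** The point holds for the women's two outcomes, self-reported exposure and salivary cotinine. As written, the inclusion criteria admit women who are expected to deliver before the measurement: those trained after about 31 weeks if delivery is at 40 weeks, or after about 28 weeks if it is at 37. These limits need only the stated two months and an assumed length of pregnancy.

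The consequence is reduced precision and an endpoint that mixes pregnant and postpartum women. The article supports neither a claim of certain bias nor any effect on the men's scores.

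How many couples are affected cannot be derived from the document. The range of about 16% to 36% is an illustration under uniform enrolment and delivery at exactly 40 weeks. It would be smaller if centres enrol mostly early in pregnancy and larger if they enrol late. The problem is foreseeable and cheap to prevent before enrolment, so it should be corrected.

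**What to change.** Add one inclusion criterion: gestational age at pre-test must leave room for training and the two-month post-test before term. About 28 weeks or less is an example that follows from the follow-up length. At 28 weeks, the post-test falls at 28 + 8.7 = 36.7 weeks if training is immediate, and under the simulation's assumptions fewer than 1% deliver first. If a gap before training is expected, lower the limit by that gap.

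In the same edit, state whether "the pregnant termination" includes delivery, so that the exclusion and the outcome definition agree for the few women who still deliver early.

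The change takes one eligibility line and one clarifying phrase. The price is a smaller pool of eligible couples, and the trial will have no data on couples first seen in late pregnancy.

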#### Exclusion criteria

The exclusion criterion is not completing the intervention for any reason, the smoker men who are not with their pregnant wives for more than one week, the pregnant termination, and the death of the spouse or immigration and active smoker women and presence of other sources of exposure such as other smokers at home, smoke exposure at work, women’s active smoking, etc.

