##### Data analysis

We will apply X2 and independent T test to analysis our data by using SPSS version 21.

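### Not completing the intervention is an exclusion criterion that only the randomised intervention arm can meet, so the group comparison can be biased

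*Protocol article*

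**What the plan says.** The section on Phase III (implementation of the educational intervention) sets up a randomised trial: "Participants randomly will allocate into two groups". On the comparator it says that the "control group will not receive any intervention, but they follow as same as experimental group". Controls get the material only after the comparison is over: "For ethical issues all educational material will offer them at the end of study".

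The programme extends over time. The section on follow up and maintaining education states "After training, for two months at the end of each week, an alert SMS will be sent to the participants", and the Plain English summary places the outcome assessment at the end of that period: "Two months after the training in the post-test phase, the questionnaire will be completed again by men".

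The Exclusion criteria section begins "The exclusion criterion is not completing the intervention for any reason". It continues with "the smoker men who are not with their pregnant wives for more than one week, the pregnant termination, and the death of the spouse or" migration, and then with active smoking by the woman and other sources of exposure. The Data analysis section is one sentence: "We will apply X2 and independent T test to analysis our data by using SPSS version 21".

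**The concern.** An eligibility criterion should be decidable before allocation and should apply equally to both arms. This one does neither. A man can fail to complete the programme only once he has been assigned to it, and a control has no programme to leave unfinished. Applying the rule therefore takes participants out of one randomised arm on the basis of their behaviour after randomisation.

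Men who skip the lecture or abandon the programme may be those least inclined to change. Dropping them would leave a more motivated intervention group to compare with controls who have not been filtered in this way. Knowledge, attitude and practice scores, reported cigarette exposure and salivary cotinine could then all look better even if the programme did nothing. Cotinine is planned only after the intervention (Data collection method), so no baseline cotinine value could show whether the excluded couples differed.

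**Working it through.** **Step 1: does the rule act on one arm only?** Three statements settle this.

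- Allocation is random, and controls receive no intervention (Phase III).
- The programme consists of a lecture, pamphlets, training of the wife and two months of weekly messages (Phase II and the follow-up section), so completion is known only after allocation.
- Non-completion for whatever reason leads to exclusion (Exclusion criteria).

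Together they mean that this criterion can be met only after randomisation and only in the intervention arm. Nothing in the article restores such participants to the comparison.

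**Step 2: how large could the bias be?** The article has no figure to reproduce: it states no sample size, SD, expected effect or dropout rate. Everything below is an illustration on assumed inputs.

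Model: no true effect; outcome with SD 1 in both arms; each participant has a latent, normally distributed propensity to complete, correlated ρ with a good outcome. The intervention arm loses its lowest fraction d on that propensity, and the control arm loses nobody under this rule. With z the standard normal quantile of d and φ the normal density, the truncated-normal mean gives

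bias (SD units) = ρ × m, where m = φ(z) / (1 − d).

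For d = 0.20: z = −0.8416, φ(z) = 0.2800, m = 0.2800 / 0.80 = 0.350. With ρ = 0.3 the bias is 0.3 × 0.350 = 0.105 SD.

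**Step 3: type I error for that case.** Assume 100 randomised per arm, so 80 remain in the intervention arm.

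- Variance among those retained: 1 − ρ² × m × (m − z) = 1 − 0.09 × 0.350 × 1.192 = 0.962.
- True standard error of the difference: √(0.962/80 + 1/100) = 0.1484.
- Pooled standard error used by the t test: √[0.983 × (1/80 + 1/100)] = 0.1487, where 0.983 = (79 × 0.962 + 99) / 178.
- The test rejects beyond 1.96 × 0.1487 = 0.2915. Upper tail: 1 − Φ((0.2915 − 0.105)/0.1484) = 1 − Φ(1.257) = 0.104. Lower tail: Φ((−0.2915 − 0.105)/0.1484) = 0.004.
- Total: about 10.8%, against a nominal 5%. A simulation of 4,000 trials gave 11.1%.

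**Step 4: the range.** The same formulas give:

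| Excluded (d) | ρ | Bias (SD) | Type I error, 50 per arm | Type I error, 100 per arm |
|---|---|---|---|---|
| any shown | 0 | 0 | 5.0% | 5.0% |
| 5% | 0.2 | 0.022 | 5.1% | 5.3% |
| 5% | 0.5 | 0.054 | 5.8% | 6.7% |
| 10% | 0.2 | 0.039 | 5.4% | 5.8% |
| 10% | 0.5 | 0.097 | 7.7% | 10.4% |
| 20% | 0.2 | 0.070 | 6.2% | 7.5% |
| 20% | 0.3 | 0.105 | 7.8% | 10.8% |
| 20% | 0.5 | 0.175 | 13.3% | 22.1% |
| 30% | 0.2 | 0.099 | 7.3% | 9.8% |
| 30% | 0.5 | 0.248 | 20.9% | 37.2% |

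The bias does not shrink as the trial grows, so the false-positive rate rises with sample size.

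**Step 5: what ρ means.** Here ρ is the correlation with the latent propensity, not with the yes/no fact of non-completion. If the correlation were with the yes/no variable, the bias would be r × √(d/(1 − d)). At r = 0.3 and d = 0.20 that is 0.3 × √0.25 = 0.15 SD. Any quoted size has to say which correlation is meant.

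**The case against.** Several objections have force.

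- **Direction is not established.** The article gives no reasons for non-completion and does not link it to outcome. Much of the package is received passively, and what counts as completing it is not defined. A reader might infer that the result is certain to favour the programme. The text supports only that it can be biased, plausibly in that direction. This stands.
- **Not every exclusion is one-sided.** End of pregnancy, death and migration can remove control couples too, so it would be wrong to say that completers are compared with every randomised control. The husband's absence for more than a week carries no timing and may be a baseline criterion, as may other smoke sources. A reader might also suppose that trained women would report such sources more often after allocation, but the article does not say when they are ascertained, so that is conjecture. This stands too, and it confines the point to the non-completion clause.
- **The analysis set may be defined in a plan that is not shown.** Silence on intention to treat is not a fault in a condensed article, and none is alleged. The exclusion rule, however, is stated outright, and an analysis set defined later could not recover a questionnaire or saliva sample that was never collected.
- **The word intervention may loosely mean the study.** Phase III says that controls receive none, which tells against this reading. Even if it were accepted, participants would still be excluded after randomisation.
- **Small dropout does little harm.** At 5% excluded and ρ = 0.2, the type I error is 5.3% at 100 per arm. That is true, but nothing in the article limits dropout to that level.

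**Conclusion.** The non-completion clause is wrong as written: a post-randomisation event that only one arm can have is used as an exclusion criterion, and the comparison of randomised groups can be biased by it. This follows directly from the article's own statements and needs no assumed figures.

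Size and direction do depend on assumptions. Bias towards the programme is plausible if less motivated men drop out, and it is zero if completion is unrelated to outcome. Under the latent-propensity model, with no true effect, 10–30% excluded and a correlation of 0.2–0.5, the spurious benefit is about 0.04–0.25 SD. These figures show what the rule could do; they are not estimates for this trial.

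**What to change.** - Delete non-completion of the intervention from the exclusion criteria, and report completion as adherence.
- Apply the baseline criteria (active smoking by the woman, other exposure sources, habitual absence of the husband) before randomisation and identically in both arms.
- Seek the two-month questionnaire and saliva sample from couples who do not complete the programme, and analyse them in their allocated arm.
- Keep any completers-only comparison as a sensitivity analysis.
- Where death, migration or end of pregnancy makes an outcome unobtainable, count the couple in its allocated arm as having missing outcome data, reported by arm, and not as an eligibility failure.

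Under the model above, collecting and analysing non-completers' outcomes as allocated brings this source of bias to zero and the type I error back to 5%. The cost is a wording change and some extra follow-up contact with couples who stop attending. The follow-up schedule already exists, because controls are followed in the same way. The estimated effect may be somewhat smaller.
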